# An exercise and patient education intervention to reduce pain and physical limitations in adults with acetabular dysplasia: study protocol for a process evaluation integrated within a randomised controlled trial (the MovetheHip trial)

**DOI:** 10.1186/s13063-024-08262-y

**Published:** 2024-06-24

**Keywords:** Hip pain, Training, Self-management, Mechanisms of change, Acceptability, Implementation, Context

## Abstract

**Background:**

The Movethehip trial investigates the effectiveness of an exercise and patient education intervention for adults with acetabular dysplasia. The intervention involves eight tailored one-to-one sessions with trained providers who employ supportive feedback tools. The present protocol reports a planned process evaluation, which aims to determine how the intervention functions by examining the implementation of the intervention (process, dose and reach), its acceptability, mechanisms of change and the influence of contextual factors.

**Methods:**

Two hundred trial participants aged 18–50 years will be recruited from a University Hospital in Denmark and randomised to the intervention or control group. Approximately ten providers will deliver the intervention. The process evaluation adopts a concurrent mixed-methods design. The implementation will be assessed using self-report questionnaires (at baseline and 6-month follow-up), training records and semi-structured focus group interviews with intervention providers (*n* = 10) and healthcare managers (*n* = 4–6). The mechanisms of change will be explored through semi-structured one-to-one interviews (at baseline and 6-month follow-up) with 15–20 purposefully sampled participants and by measuring changes in health outcomes (self-reported pain, physical functioning and quality of life completed at baseline and at 3- and 6-month follow-up). Additionally, change will be measured through an explorative examination of associations between dose and change in health outcomes, applying simple linear regression models. The acceptability of the intervention and the influence of contextual factors will be explored through one-to-one participant interviews and focus group interviews with 4–6 healthcare managers. The interviews will focus on expectations, experiences, events, personal understandings and interaction with interpersonal and organisational aspects. Interview data will be analysed using theoretical thematic analyses, and findings will be merged with quantitative data and reported jointly on a theme-by-theme basis.

**Discussion:**

The process evaluation conducted as part of the MovetheHip trial will illuminate how the intervention functions, and if the intervention is proven effective, the findings of the evaluation will contribute to pinpoint how the intervention may be optimised to facilitate future up-scaling and implementation.

**Trial registration:**

The MovetheHip protocol was approved by the Committee on Health Research Ethics in the Central Denmark Region. ClinicalTrials, NCT04795843. Registered on 20 March 2021.

**Supplementary Information:**

The online version contains supplementary material available at 10.1186/s13063-024-08262-y.

## Background

Acetabular dysplasia is a condition characterised by reduced acetabular coverage of the femoral head [1]. It is most commonly seen in young-to-middle-aged persons [2]. Pain and physical limitations imposed by acetabular dysplasia may be improved surgically by periacetabular osteotomy (PAO) [2–4]. However, several barriers to surgery have been reported [5–7]. These barriers include having a Body Mass Index above 25, being above 45 years or having hip osteoarthritis. Thus, a PAO may not be offered as a treatment option to persons with these characteristics due to a heightened risk of adverse outcomes [5–7]. In addition, some eligible persons may not be willing to undergo surgery. Both candidates for surgery and those who do not undergo surgery may experience pain and detrimental effects on their physical and mental well-being [8, 9]. Such effects may include feeling controlled by their hip pain, being limited in their participation in social and physical activities of everyday life, and worrying about their future [8].

In persons not undergoing surgery, exercise may potentially be an alternative to reduce pain and improve physical functioning [10–12]. However, the evidence base for exercise interventions aiming to treat symptoms in acetabular dysplasia is weak. Only small pilot and feasibility studies have been published [10–12], and none of these studies focused on people not undergoing surgery [10–12]. Furthermore, study limitations were described. These limitations include insufficient intervention description and low recruitment or exercise adherence. Furthermore, all studies failed to monitor motivation for exercise and physical activity in everyday life [10–12]. However, participants’ motivation for exercise and physical activity is critical [13], especially in persons with acetabular dysplasia who experience a lack of control and are limited in relation to social and physical activities [8]. A range of theories have been developed to understand the complexity of motivation, including self-determination theory [14, 15] and motivational interviewing [16]. Evidence supports that interventions based on these two theories effectively promote physical activity [17–19].

We developed an intervention that integrates motivation for exercise and physical activity for adults with acetabular dysplasia who are not undergoing surgery. The intervention was prepared in accordance with Medical Research Council (MRC) guidance on the development and evaluation of complex interventions [20]. We conducted a feasibility study on this intervention [9]. This feasibility study confirmed that it was feasible to conduct a full-scale randomised controlled trial (RCT) with an integrated process and economic evaluation entitled the MovetheHip trial. The protocol for the MovetheHip trial has been reported elsewhere [21]. The present protocol reports the planned process evaluation following the MRC guidance on process evaluations [22, 23].

## Programme theory

### Mechanisms of change

The MovetheHip intervention aims to reduce pain and physical limitations by enhancing hip muscle strength through physical exercises and physical activity, while also assisting participants in managing their condition in everyday life.

Motivation for exercise and physical activity is critical, and the participants are considered more vulnerable than background populations without pain because they have to sustain motivation for exercising despite experiencing pain and discomfort [13]. Therefore, the mechanisms of change are rooted in self-determination theory and motivational interviewing. Furthermore, being rooted in the self-determination theory, the intervention incorporates the psychological determinants of autonomy, competence and relatedness [14, 15]. By targeting these determinants, we hypothesise that the intervention will shift behaviour from motivation by external control towards more integrated regulated motivation [15, 24] leading to integration of exercises and physical activity into participants’ everyday lives, thereby increasing their physical and mental well-being [13–15] (Fig. 1).

**Fig. 1 Fig1:**
[figure not shown]
MovetheHip logic model with implementation, acceptability, mechanisms of change and contextual factors

### MovetheHip intervention components

The intervention is delivered by providers who are trained in self-determination theory and motivational interviewing. It involves two components: an exercise programme and patient education.

#### MovetheHip exercise programme

Eight supervised physical one-to-one sessions will be delivered in the course of 6 months [9, 21], and each session takes 30–45 min (time is recorded). In the supervised sessions, an intervention provider will guide the participant through four exercises [9, 21]. These exercises are (1) a supine plank exercise, (2) a side-lying plank exercise, (3) a squat exercise and (4) a one-leg stability exercise. Each exercise may be performed at one of three predefined difficulty levels, with exercise repetitions ranging from 5 to 20. All participants will start at the lowest difficulty level (C) and move to higher levels (B and A) over time based on their Borg CR10 Scale score [25] and individual preferences, goals and resources. Similarly, individual adjustments will be made with respect to exercise repetitions. The participants will be encouraged to perform a minimum of three weekly training sessions at home. Each session takes approximately 20–30 min.

#### MovetheHip patient education

The participants will also receive one-to-one verbal patient education at each supervised session based on their individual needs [9, 21]. The education will focus on acetabular dysplasia, the rationale and importance of being physically active and exercising regularly. Additional educational topics include tissue tolerance and pain mechanisms, gains from exercise and the association between being overweight and experiencing pain.

Part of the patient education will include encouraging participants to fit exercises and physical activity into their everyday lives. They will receive support to manage any experienced barriers between the supervised sessions and be encouraged to adjust the exercises to their level of functioning, time available and personal resources. The counselling provided will be non-judgemental, respectful and empathic, aiming to enhance the participants’ motivation to integrate exercises and physical activity into their everyday lives [13, 16].

### MovetheHip implementation strategy

The implementation strategy is empirical, based on observations made in an orthopaedic outpatient clinic at a University Hospital in Denmark and in public and private clinics in Denmark.

#### Recruitment of participants

Persons with symptoms and a radiograph consistent with acetabular dysplasia will be referred from general practice to an outpatient clinic at a Danish University Hospital. At the clinic, an orthopaedic surgeon will provide a diagnosis and, together with the person, decide on the necessity of surgery. As part of this procedure, the participants will be recruited by orthopaedic surgeons at the outpatient clinic [9, 21]. Surgeons were involved in the planning of recruitment procedures and the drafting of written recruitment material. The recruitment material includes a short checklist of procedures, contact information for the principal investigator (first author), a screening form and written material for the participants. The material will be placed in each clinic room and will remain accessible anytime for surgeons. The principal investigator will hold regular meetings with the surgeons, discussing the eligibility of individual participants.

#### Identification of intervention providers

The intervention providers will be physiotherapy students from a university college in Denmark [21]. Written and oral advertisement materials are shared with second-year students, and selected students will serve as intervention providers until they graduate. Three months before graduation, new students will gradually replace former intervention providers over a 2-month period until all participants have completed their intervention period.

#### Training of intervention providers

Intervention providers will deliver the intervention under the supervision of an expert team of physiotherapists (a senior lecturer, the first and fourth authors) [9, 21]. Each provider will receive two 2-h training workshops and 1 h of one-to-one supervision per participant to teach providers how to deliver the intervention and counsel participants in line with self-determination theory and motivational interviewing. The providers will be trained to spot any signs of barriers and lack of preparedness for exercise and for engaging in physical activity and will learn how to respond to distress or need for support in a manner that satisfies the need for autonomy, competence and relatedness. During the intervention period, the students and the expert team will attend regular evaluation meetings to ensure that the intervention providers feel prepared to deliver an individually tailored intervention.

### The influence of the context

The mechanisms of change will be underpinned by an ecological view of change. We hypothesise that characteristics of the context (i.e. personal, interpersonal and organisational factors) will interact with the fulfilment of the need for autonomy, competence and relatedness, ultimately influencing the quality of expected and experienced behaviour [26].

## Process evaluation aim

The present protocol reports the planned process evaluation, which aims to determine how the intervention functions by examining the following three domains: (I) Implementation of the intervention (process, dose and reach), (II) Acceptability of the intervention, (III) Mechanisms of change and the influence of contextual factors across the three domains.

### Process evaluation research questions

The domains of the process evaluation will be examined by answering the following overarching research questions (further details are provided in Table 1):Is the intervention delivered with fidelity, and how do contextual characteristics structure fidelity?Is the intervention acceptable to the participants, the intervention providers and the healthcare managers, and how do contextual factors interact with acceptability?Does the intervention work in accordance with the proposed mechanisms of change, and how do contextual characteristics influence these mechanisms?

**Table 1 Tab1:** The process evaluation domains in relation to research questions, data sources and procedures

Domains	Research questions	Data sources	Procedures	When	Informants
**Implementation**	How do observations and experiences (context) relate to tailoring to each participant, and how do they relate to intervention fidelity?	Focus group interviews	Interview led by the last author (evaluation meetings)	Throughout trial	Intervention providers (*n* ≈ 10) and expert team^c^ (*n* ≈ 3)
		Online survey	Self-report: fidelity as the extent which intervention was delivered, 100 mm VAS	Six months	Intervention providers (*n* ≈ 10)
**Implementation**	Do baseline characteristics differ between participants who received high and low intervention doses and in participants and non-participants (intervention reach)?	Online record	Self-report	Baseline	Participants (*n* ≈ 100)
		Online record	Clinician registration: radiographical variables	Baseline	Participants (*n* ≈ 100)
		Online rating scale^b^	Self-report: exercise dose	Six months	Participants (*n* ≈ 100)
**Implementation** **(explorative)**	How does dose relate to changes in health outcomes?	Online PROM^a^	Self-report: pain, physical functioning and QOL	Baseline, 3 and 6 months	Participants (*n* ≈ 100)
		Online rating scale^b^	Self-report: exercise dose	Six months	Participants (*n* ≈ 100)
**Acceptability**	How do contextual factors relate to expectations and behavioural experiences?	1:1 semi-structured interviews	Interview led by the first author	Baseline and 6 months	Participants (*n* ≈ 15–20)
**Acceptability**	How prepared do providers feel to deliver the intervention?	Focus group interviews	Interview led by the last author (evaluation meetings)	Throughout trial	Intervention providers (*n* ≈ 10) and expert team^c^ (*n* ≈ 3)
**Acceptability**	How do contextual factors relate to perceptions of a forthcoming implementation?	Focus group interview	Interview led by the last author	When 50% of the participants have been recruited	Healthcare managers and practice consultants (*n* ≈ 4–6)
**Acceptability** **(explorative)**	Does the reason for deselecting surgery moderate dose?	Online rating scale^b^	Self-report: exercise dose	Six months	Participants (*n* ≈ 100)
		Online record	Clinician registration: reason to deselect surgery	Baseline	Participants (*n* ≈ 100)
**Mechanisms of change**	Does intervention functioning relate to a change in health outcomes?	1:1 semi-structured interviews	Interview led by the first author	Baseline and 6 months	Participants (*n* ≈ 15–20)
		Online PROM^1^	Self-report: pain, physical functioning and QOL	Baseline, 3 and 6 months	Participants (*n* ≈ 100)
**Mechanisms of change**	How do contextual factors structure intervention functioning?	1:1 semi-structured interviews	Interview led by the first author	Baseline and 6 months	Participants (*n* ≈ 15–20)

*PROM* Patient-reported outcome measure, *QOL* Quality of Life, *VAS* Visual analogue scale

^a^Self-reported pain, physical functioning in sports and recreation and quality of life measured by the Copenhagen Hip and Groin Outcome Score and physical functioning measured with the Short version of the International Hip Outcome Tool

^b^Exercise Adherence Rating Scale

^c^A senior lecturer, the first and fourth authors

## Methods

### Overarching research design

The overarching study design is a parallel-group superiority RCT with integrated process and health economic evaluation [21] designed in line with MRC Guidance principles [20]. The RCT follows the Standard Protocol Items: Recommendations for Interventional Trials statement [27] (Additional file 1). The process evaluation will follow a concurrent design with data collection and analyses being completed during similar time frames [28] (Fig. 2). The trial participants will be 18–50 years old and will have radiographically verified acetabular dysplasia and have experienced hip pain for a minimum of 3 months [21]. The participants will be dichotomised into either eligible but unwilling to undergo a PAO or not eligible for the PAO [21]. Further information on the study setting, eligibility criteria, sample size, etc., is reported in the RCT protocol [21]. In brief, to obtain sufficient statistical power, the RCT will recruit a minimum of 85 participants to the intervention group and 85 to the control group (usual care). Usual care includes one oral consultation provided by the first author on self-management of hip symptoms, including advice about staying physically active and exercising and, if relevant, advice to lose weight [21]. All intervention group participants will be included in the generation of process data. The RCT aims to investigate the effectiveness and cost-effectiveness of exercise and patient education compared with usual care [21].

**Fig. 2 Fig2:**
[figure not shown]
Flowchart of the MovetheHip trial proceedings and process evaluation. Abbreviations: SDT, self-determination theory; MI, motivational interviewing; HAGOS, Copenhagen Hip and Groin Outcome Score; iHOT-12, Short version of the International Hip Outcome Tool; PAO, periacetabular osteotomy

### Implementation

We will conduct a multi-component examination of the implementation of the intervention, including process, fidelity, dose and reach [21]. We will examine the implementation process by describing the required structures and resources, and we will measure fidelity as the degree to which the intervention is delivered as intended. Dose will be measured as the number of completed supervised and home-based exercise sessions. High dose is defined as completing a minimum of 75% of scheduled training sessions, medium as completing 50–74% and low as completing less than 50% [21]. Additionally, we will measure the dose using the exercise adherence rating scale (EARS) [29, 30]. Reach will be examined by describing baseline participant characteristics in those receiving a high compared versus a low dose, and by comparing the age and sex of participants with those of non-participants. In an additional explorative analysis, we will examine if the dose is associated with changes in health outcomes.

### Acceptability of the intervention

We will explore acceptability by examining the extent to which the participants, intervention providers and healthcare managers consider the intervention to be appropriate based on their anticipated (prospective acceptability) or experienced responses to the intervention and received training (concurrent and retrospective acceptability) [31]. In an additional explorative analysis, we will explore if the reason for deselecting surgery (i.e. dichotomised into surgeon’s decision (not a surgical candidate) and participant’s decision (unwilling to undergo surgery)) moderates dose.

### Mechanisms of change

Mechanisms of change will be assessed by analysing how participants interact with the intervention activities to facilitate change in health outcomes. We will examine if autonomy, competence and relatedness relate to motivation and change in health outcomes and study the influence of contextual factors [22, 23].

### Contextual factors

Contextual factors include events and a socioecological view of personal, interpersonal and organisational factors interacting with the implementation, acceptability and mechanisms of change. By adopting a socioecological perspective, we will consider the implication of individual attitudes and behaviour and the quality of bonds to the intervention providers and support from family and friends. Furthermore, we will consider the impact of organisational support to gain additional knowledge on how processes may be optimised to facilitate any up-scaling of the intervention.

### Data sources

The following sections outline data collection methods and sources relevant to the process evaluation. The timing and relation to the research questions are described in Table 1. Trial procedures are described in Fig. 3. The trial protocol paper details all wider measures obtained as part of the effectiveness trial [21].

**Fig. 3 Fig3:**
[figure not shown]
Schedule of procedures for the MovetheHip randomised controlled trial (SPIRIT figure)

#### Participant data measured

Orthopaedic surgeons and research assistants will measure and register baseline participant characteristics as reported in the trial protocol [21]. The baseline data will be used to describe intervention reach.

#### Online participant survey

Participants will enter baseline data using a survey option in a Research Electronic Data Capture (REDCap) database. Baseline process data include sex, age, duration of hip symptoms, educational level, employment status, cohabiting status and level of physical activity [21]. These data will be used to examine intervention reach as aforementioned.

#### Online participant-reported health outcome measures (health outcomes)

Self-reported pain, physical functioning in sports and recreation and quality of life will be measured using the Copenhagen Hip and Groin Outcome Score (HAGOS) [32]. Self-reported hip-related quality of life will be measured using the Short version of the International Hip Outcome Tool (iHOT-12) [33]. These health outcomes will be used to examine the underlying mechanisms of change by exploring how any changes in health outcomes are related to satisfaction of psychosocial needs and motivation.

#### Participant training records

Intervention dose is the number of completed training sessions (supervised and home-based) and the more comprehensive measure of doses received using the EARS [21]. The participants will prospectively register the number of completed training sessions using a weekly logbook and register with the EARS [29] the extent to which the four exercises described in the exercise programme are completed. The dose data will serve to examine intervention reach as aforementioned.

#### Online fidelity survey

Intervention providers will use a 100-mm visual analogue scale (VAS) in a REDCap survey form to measure their ability to deliver specific content of the intervention, ranging from not possible (0) to always possible (100). The intervention components describe the ability to deliver the following: (1) use the Borg CR10 to determine the difficulty level and repetitions of exercises; (2) use the participant’s expressions of exercise acceptability to determine difficulty level and repetition; (3) use the intervention manual to determine correct exercise performance; (4) council participants about pain mechanisms in acetabular dysplasia, give advice on physical activity, monitor weight loss (if relevant) and deliver support to increase exercise adherence. The data will be used to examine intervention tailoring as an integral aspect of the implementation process.

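### The provider fidelity rating is worded as ability to deliver, while the plan defines fidelity as extent of delivery, so the rating can overstate delivery and cannot by itself quantify it

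*Protocol article*

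**What the plan says.** The first research question in the protocol article is "Is the intervention delivered with fidelity, and how do contextual characteristics structure fidelity". Under Methods, Implementation, the authors commit to a definition: "we will measure fidelity as the degree to which the intervention is delivered as intended". Table 1 lists the provider survey in the same sense: "Self-report: fidelity as the extent which intervention was delivered, 100 mm VAS", completed at six months by about 10 providers. The row it belongs to asks "How do observations and experiences (context) relate to tailoring to each participant, and how do they relate to intervention fidelity" and also names focus groups with providers and the expert team as a source.

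The Online fidelity survey section describes the instrument itself. Providers use the scale "to measure their ability to deliver specific content of the intervention, ranging from not possible (0) to always possible (100"), and the items are introduced with "The intervention components describe the ability to deliver the following". Four content areas follow: use of the Borg CR10, use of the participant's expressed acceptability, use of the manual, and counselling. The section ends: "The data will be used to examine intervention tailoring as an integral aspect of the implementation process".

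Two other records bear on delivery. Completed supervised and home sessions are counted as dose. For the length of supervised sessions, the exercise programme section notes that "time is recorded".

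**The concern.** A rating of what was possible and a rating of what was done are different measurements. A provider who could always have used the Borg CR10, but used it in only some sessions, can truthfully mark the top of the scale. The analysis section plans descriptive statistics for implementation data. A mean of these scores, read with the Table 1 description, would be taken as the extent delivered although the question concerned possibility.

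This matters for the first research question and for reading the trial result. If the trial shows little difference, readers will ask whether the content reached participants. The Discussion itself names maintaining fidelity as a challenge. Providers are students who are replaced as they graduate, and controls also receive advice on activity, exercise and, where relevant, weight. Variation in what was delivered is therefore plausible and would affect interpretation.

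**Working it through.** The plan gives no figure to reproduce. The check compares its descriptions and asks what a score can imply.

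**1. The descriptions side by side**

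| Place in the protocol article | What is rated |
|---|---|
| Methods, Implementation | Degree delivered as intended |
| Table 1, provider survey row | Extent delivered, on the VAS |
| Online fidelity survey, construct and item stem | Ability to deliver |
| Online fidelity survey, anchors | Not possible (0) to always possible (100) |
| Online fidelity survey, stated use | Tailoring |

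The first two concern what happened. The construct, stem and anchors of the instrument concern what could happen. The word *always* brings in frequency, but it qualifies possibility.

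**2. What a score implies**

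Let *s* be the share of applicable sessions in which the content could be delivered, and *d* the share in which it was. Content that was delivered must have been possible, so *d* ≤ *s*. Assume that providers recall accurately and read the scale as a share, so that score = 100 × *s*. Then:

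- score 0: *d* = 0;
- score 50: *d* lies between 0 and 50%;
- score 100: *d* lies between 0 and 100%.

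For example, *s* = 100% and *d* = 50% gives a score of 100, twice the true share. These are logical limits, not estimates. They show that the score is an upper bound: a low score is informative about non-delivery, while a high score does not establish delivery.

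**3. Whether other sources fill the gap**

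- Focus groups cover challenges, adaptations and perceived quality of delivery. They help explain fidelity but give no degree of it.
- Completed sessions show whether a session took place, not what was in it.
- The Exercise Adherence Rating Scale is the participant's report on carrying out the four exercises, not on what the provider delivered.
- Session time is recorded, but no section gives it a role in fidelity.

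No described source measures the content delivered within sessions.

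**4. Scale of the delivery being rated**

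About 100 intervention participants × 8 sessions = 800 scheduled supervised sessions. In January 2024, 76 of 200 participants were enrolled. If they split equally between groups, 76 / 2 = 38 were in the intervention group, with 38 × 8 = 304 scheduled sessions. That left 800 − 304 = 496, or 496 / 800 = 62%, belonging to participants not yet enrolled.

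**The case against.** The strongest reply is that fidelity does not rest on this scale alone. Table 1 pairs it with focus groups running throughout the trial, and those ask directly about quality of delivery and adaptations. Session counts and adherence ratings help separate sessions not received from sessions received without benefit. All of this stands. A reader might infer that the fidelity question cannot be answered at all, or that a null trial result could not be interpreted; the documents support neither. What is missing is narrower: a quantity for content delivered within the sessions held.

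A reader might also infer that a provider who delivered everything with difficulty would score low. The anchors do not support this. They run from not possible to always possible, not from hard to easy, so content delivered every time should score near 100. The bias is towards overstating delivery.

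It is also fair to say that the questionnaire is not shown, that the article is a condensed account, and that the survey section assigns the data to tailoring rather than promising to report them as fidelity. The actual form may be closer to Table 1. That limits certainty about the instrument, but the descriptions still conflict, and Table 1 does label the scale as fidelity.

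Finally, a plain count over all sessions would penalise intended tailoring: education follows individual needs, and weight content applies only where relevant. This objection stands, and it shapes the remedy.

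**Conclusion.** The point holds as a mismatch between definition and instrument. The plan defines fidelity, and this scale, as extent of delivery, but words the scale as ability to deliver. As worded, the only quantitative fidelity measure described can overstate delivery and cannot by itself quantify the degree delivered.

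The size of any overstatement cannot be derived from the document; only its direction and the upper-bound property follow. The conclusion assumes that the survey section describes the form in use. It does not depend on how many ratings each provider gives. Table 1 lists about 10 informants, and one rating each would be an assumption; ratings per participant would raise the count without changing what is measured.

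The consequence is confined to the process evaluation, chiefly its first research question. Sample size, power and the randomised comparison are unaffected.

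**What to change.** Make the Implementation section, Table 1 and the Online fidelity survey section describe one construct.

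- **Remaining data collection:** re-anchor each item to the share of sessions in which the content was delivered when it applied, with 0 = none and 100 = all applicable sessions. Where content never applied, record the item as not applicable, so that tailoring and conditional content are not scored as infidelity.
- **Responses already collected:** report those given under the existing wording as perceived deliverability, not fidelity. Do not re-ask former providers, whose recall of session frequencies could be years old.
- **Reporting:** beside the fidelity result, present the number of completed supervised sessions out of 8 and the recorded session time. Both are already collected and serve as context, not as substitutes for content.

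If the form in use already asks about extent delivered, correcting the survey section's description is enough.

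The cost is a change of wording in the REDCap form and a shorter fidelity series. On the January 2024 enrolment figures and an equal split, sessions of participants still to be enrolled made up about 62% of those scheduled; the share falls the later the change is made.
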